**Figure 3 figure3:**
[figure not shown]
Life’s Essential 8 includes key areas for improving and maintaining cardiovascular health as defined by the American Heart Association.

Quality of life is measured via short (15-minute) and long (30-minute) web-based surveys. Long web-based surveys, administered at baseline, 6 weeks, and 6 months, take 30 minutes to complete and assess psychosocial status and other health behaviors using the EPDS, General Anxiety Disorder Assessment, Pittsburgh Sleep Quality Index, Perceived Stress Scale, Brief Resilience Scale, Scale of Perceived Social Support, Posttraumatic Stress Disorder Checklist for *DSM-5* (*Diagnostic and Statistical Manual of Mental Disorders* [Fifth Edition]), and smoking status. Short web-based surveys, administered at 2 weeks and 3 months post discharge, take 15 minutes to complete and assess psychosocial status using EPDS, General Anxiety Disorder Assessment, and Pittsburgh Sleep Quality Index (Table 3).

**Table 3 table3:** Data are collected via short and long REDCap^a^ surveys, and in-person measurements are taken by this study’s team^b-e^.

Data collection instruments and measures	Long web-based survey, 30-min^b^	Short web-based survey, 15-min^c^	In-person measurements^d^
EPDS^e^	✓	✓	
GAD-7^f^	✓	✓	
AHA^g^ My Life Check (Heart Score)^h^	✓		
PCL-5^i^	✓		
PSS-10^j^	✓		
PSQI^k^	✓	✓	
BRS^l^	✓		
Perceived social support	✓		
Hemoglobin A_1c_^m^			✓
Cholesterol			✓
Weight and height			✓
Blood pressure			✓
Smoking status	✓		

^a^REDCap: Research Electronic Data Capture.

^b^Baseline, 6 weeks, and 6 months.

^c^2 weeks and 3 months.

^d^Baseline, 3 months, and 6 months.

^e^EPDS: Edinburgh Postnatal Depression Scale.

^f^GAD-7: General Anxiety Disorder Assessment.

^g^AHA: American Heart Association.

^h^My Life Check is only completed in baseline and 6–month-long surveys.

^i^PCL-5: Posttraumatic Stress Disorder Checklist for DSM-5 (Diagnostic and Statistical Manual of Mental Disorders [Fifth Edition]).

^j^PSS-10: Perceived Stress Scale.

^k^PSQI: Pittsburgh Sleep Quality Index.

^l^BRS: Brief Resilience Scale.

^m^Hemoglobin A_1c_: glycated hemoglobin.

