### Statistical Analysis: Analysis of the Dual Primary End Points

Preliminary statistical analysis examines baseline characteristics between study arms (LHMoms intervention vs attention control) to verify that the randomization generated comparable groups. Categorical variables are summarized as frequencies and proportions. Statistical significance is set at *P*<.05 and tested using chi-square or Fisher Exact tests for variables with low expected frequencies (eg, <5). Continuous variables are described as mean, SD, median, and IQR. Statistical significance is tested using a 2-tailed Student *t* test or Wilcoxon Rank Sum for variables with unequal variance or skewed distributions.

The primary outcome of PPDS is operationalized as the presence or absence of PPD symptoms as indexed by an EPDS score greater than or equal to 9 (EPDS >9) at 6 months post partum (Table 4). Linear mixed models, designed to account for the nonindependence of observations within the same person that is inherent to repeated measures designs, are used to estimate the mean EDPS score with 95% CIs and make group comparisons between the LHMoms intervention and attention control at baseline and 6 months post partum. This approach enables an intention-to-treat analysis whereby all participants randomized into the trial are included in the primary analysis regardless of the number of sessions completed due to the flexibility of linear mixed models to handle the presence of missing data. Baseline characteristics associated with PPDS in univariate regression models (eg, parity) or group imbalance detected at baseline are included in linear mixed models as relevant covariates.

**Table 4 table4:** Primary and secondary outcomes measured in REDCap^a^ surveys assess psychosocial status and other health behaviors, as well as health care use and patient satisfaction.

Primary or secondary	Name of outcome	Specific measure to be used
Primary	PPDS^b^	EPDS^c^≥9
Primary	Cardiovascular health	LE8^d^ (continuous measure)
Secondary	Anxiety	GAD-7^e^
Secondary	Posttraumatic stress disorder	PCL-5^f^
Secondary	Perceived stress	PSS-10^g^
Secondary	Sleep	PSQI^h^
Secondary	Resilience	BRS^i^
Secondary	Social support	Perceived Social Support Scale
Secondary	Health care use	Contact at 7 days; 6 weeks postpartum visit attendance
Secondary	Satisfaction with postpartum care	CSQ-8^j^
Secondary	Implementation process	Focus groups, surveys, and interviews

^a^REDCap: Research Electronic Data Capture.

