### Sample Size Determination for Primary End Points

The EPDS scores from baseline to 6 months are used to analyze PPDS in LHMoms and control arms. While we considered PPDS and LE8 as dual primary end points, we chose 1 outcome to base our sample size on, which was PPDSs as defined by an EPDS score >9. This score was specifically chosen because it is used as the screening cutoff to refer for clinical evaluation in our hospital system, as it represents the possible presence of depressive or anxiety symptoms. The rate of EPDS >9 ranges from about 30% to 40% depending on other characteristics of the clinics (we selected 33.5% as the lower tertile of this observed range for our nonintervention group in the power calculation). We project we will observe a reduction in the PPDS proportion from 33.5% in the control arm to 23% in the intervention arm. This yields a minimum detectable difference of 31.5% lower incidence of PPDS in the LHMoms intervention arm compared to the attention control arm at 6 months. Our minimum detectable difference is calculated with a sample size of approximately 450 individuals (225 per study arm), assuming a 1:1 randomization, a design effect of 1.5 to account for variance among sites and doulas, a power of .90, a 2-sided significance level of 0.05, and a 20%-25% attrition. Our recruitment projection is for a sample of 600, 300 per arm; however, we have conservatively built in a 25% attrition rate for the longitudinal study (thus powering from a 450 analytic sample), although in past studies we have achieved 80%-85% retention in studies with a longer 1-year observation period [47-50].

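### The primary PPDS outcome is defined, sized and hypothesised as a proportion, but the only primary analysis stated for it is a linear mixed model of mean EPDS

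*Protocol article*

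**What the plan says.** **Endpoint.** In the protocol article, section Statistical Analysis: Analysis of the Dual Primary End Points, the PPDS outcome "is operationalized as the presence or absence of PPD symptoms as indexed by an EPDS score" cutoff at 6 months. Table 4 lists it as a cutoff and labels the other primary outcome, LE8, a continuous measure.

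**Analysis.** The next sentence of that section says that linear mixed models "are used to estimate the mean EDPS score with 95% CIs and make group comparisons between the LHMoms intervention and attention control"; the time points named for this are baseline and 6 months. The section gives this model primary status: all randomised participants "are included in the primary analysis regardless of the number of sessions completed due to the flexibility of linear mixed models" in handling missing data.

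**Sample size.** Sample Size Determination for Primary End Points says "we chose 1 outcome to base our sample size on, which was PPDSs as defined by an EPDS score >9". It projects a "reduction in the PPDS proportion from 33.5% in the control arm to 23% in the intervention arm", described as a "minimum detectable difference of 31.5% lower incidence of PPDS in the LHMoms intervention arm", with 225 analysed per arm, design effect 1.5, 90% power and two-sided 0.05.

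**Hypothesis.** Summary and Conclusions in the Discussion expects a rate of PPDS at least 31.5% lower at 6 months.

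**The concern.** Three of the four elements (definition, sizing and hypothesis) concern a proportion. The fourth, the model, concerns a mean. A linear mixed model of EPDS scores returns a difference in points, from which no proportion, risk difference or risk ratio can be read. A significant result would not confirm the stated hypothesis, and a null result would not refute it.

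The two quantities can part company. As an illustration per 100 participants, let 10.5 move by one point from just above the cutoff to just below it. The proportion then falls by the full 10.5 percentage points (33.5% to 23%), while the mean falls by only 10.5 × 1 / 100 = 0.105 points. Conversely, if 50 participants who are all below the cutoff score 2 points lower, the mean falls by 50 × 2 / 100 = 1 point and the proportion does not change.

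The sizing section justifies the cutoff as the screening threshold for referral in the hospital system. A mean difference does not address that threshold.

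**Working it through.** **1. Is the binary outcome tested anywhere in the article?**
- The chi-square and Fisher tests in the statistical section compare baseline characteristics.
- The univariate regression models for PPDS select covariates.
- The sample size section says that EPDS scores from baseline to 6 months are used to analyse PPDS, but names no binary model.
- Table 6 lists the percentage with PPDS in each arm as an effectiveness outcome, without a test.

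So no between-arm test of the binary outcome is stated.

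**2. The plan's own sample size.** Inputs from the sample size section: p1 = 0.335, p2 = 0.23, two-sided 0.05, power 0.90, design effect 1.5, attrition up to 25%.

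Relative reduction = (0.335 − 0.23)/0.335 = 31.3%, against 31.5% stated.

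Pooled two-proportion formula: n = [1.960·√(2p̄q̄) + 1.282·√(p1q1 + p2q2)]² / (p1 − p2)²
- p̄ = 0.2825, so √(2 × 0.2825 × 0.7175) = 0.6367
- √(0.2228 + 0.1771) = 0.6324
- n = (1.248 + 0.810)² / 0.105² ≈ 384.3, so 385 per arm
- with the design effect: 384.3 × 1.5 ≈ 577, or 578 from the rounded 385
- enrolled, with 25% attrition: 578/0.75 = 771 per arm

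The stated 225 analysed per arm (300 enrolled) is not reproduced. Of the variants tried, it matches only one-sided 0.05 at 80% power with no design effect (227 pooled, 226 arcsine, 225 unpooled).

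**3. Power of the binary comparison at the planned size.** Power = Φ{[0.105·√n − 1.248]/0.6324}
- n = 225, no design effect: Φ(0.517) = 69.8%
- effective n = 225/1.5 = 150: Φ(0.060) = 52.4%

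**4. Does the power statement carry over to the mean?** The article gives no EPDS SD, so power for the mean comparison cannot be derived from it. Under an assumed normal EPDS with equal SDs, the two rates correspond to d = z(0.77) − z(0.665) = 0.313.
- effective n = 150, no baseline adjustment: Φ(0.313 × √75 − 1.96) = 77%
- with an assumed baseline correlation of 0.3, 0.5 or 0.7: 81%, 88% or 97%

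These figures are illustrative only. The mismatch does not depend on them.

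**5. The cutoff.** The statistical section gives at least 9 and, in brackets in the same sentence, above 9. Table 4 uses at least 9. Data Collection, the sample size section and the Discussion use above 9. A score of exactly 9 is a case under one and not under the other.

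**The case against.** The best defence is that this is a condensed article and the full analysis plan may hold a binary model. That is a fair limit on the claim. A reader might infer that the trial will never test its primary endpoint; the article supports only that no such test is stated in it. The defence does not remove the point, because the article does not leave the model open. It names one, calls it the primary analysis, and that model does not match the endpoint.

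Four other inferences are tempting and should not be drawn:
- **That the 2-week, 6-week and 3-month EPDS scores go unused.** The model is described as a repeated-measures model, and the sizing text refers to scores from baseline to 6 months. Naming baseline and 6 months may only identify the reported contrasts.
- **That two rival primary analyses are on offer, to be chosen after the results.** Only one model is given, and analysts are to be blinded to condition. The fault is a mismatch between endpoint and estimand.
- **That the mean analysis is shown to be the more powerful one.** That holds under the normality assumption in step 4. The article gives no SD or correlation.
- **That calling the 6-month proportion an incidence is a further error of analysis.** The article uses incidence and prevalence loosely. This is wording and changes no test.

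It can also be said that a linear mixed model was chosen to keep participants with missing data in the analysis. A mixed logistic model is likelihood-based too and offers the same advantage, so this is no reason to leave the binary scale.

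**Conclusion.** The mismatch is established from the article's own text: a binary endpoint, a binary sample size and a binary hypothesis, with a primary model of a mean. As written, the stated hypothesis of at least a 31.5% reduction has no matching primary test in this document. This needs no assumption about the distribution of EPDS.

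The stated 90% power does not hold for the binary comparison on the plan's own inputs: it is about 52% at 225 per arm with design effect 1.5. For the mean comparison it cannot be checked. It would be about 77% only if EPDS were normal with equal SDs and no baseline adjustment. The failure of the sample size to reproduce is a separate fault, but it bears on the remedy, because analysing the endpoint as defined exposes it.

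**What to change.** Make endpoint, model, hypothesis and power statement agree, in the protocol and in the analysis plan, before analysis begins.

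**Preferred route.** Keep the binary 6-month endpoint. Analyse it with a mixed logistic model, or with a GEE using a small-sample correction because there are only 24 doulas. Include treatment, visit, treatment-by-visit, site, baseline EPDS and doula clustering, and allow for repeated measures within participant. Report the 6-month risk difference and risk ratio, standardised from the model, as the primary contrast. If a GEE is used, state how the planned attrition of up to 25% is handled, since an unweighted GEE makes a stricter missing-data assumption than a likelihood model. Make mean EPDS a named secondary analysis.

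**Alternative route.** Redefine the endpoint, hypothesis and sample size on mean EPDS, with a stated SD, baseline correlation and target difference.

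**Under the preferred route,** settle one cutoff and use it in the statistical section, Table 4, Data Collection, the sample size section and the Discussion.

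**Cost.** The model change is wording only. The EPDS data are already scheduled, no visit is added, and the Results section places analysis from September 1, 2029. The preferred route has a price to disclose: about 52% power at the planned size. Restoring 90% at the stated rates would need about 578 analysed and 771 enrolled per arm (2 × 771 = 1,542 in total, against 600 planned). The power statement must be restated under either route.

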^b^PPDS: postpartum depressive symptom.

^c^EPDS: Edinburgh Postnatal Depression Scale.

^d^LE8: Life’s Essential 8.

^e^GAD-7: General Anxiety Disorder Assessment.

^f^PCL-5: Posttraumatic Stress Disorder Checklist for DSM-5 (Diagnostic and Statistical Manual of Mental Disorders [Fifth Edition]).

^g^PSS-10: Perceived Stress Scale.

^h^PSQI: Pittsburgh Sleep Quality Index.

^i^BRS: Brief Resilience Scale.

^j^CSQ-8: Client Satisfaction Questionnaire-8.

To determine changes in the second primary outcome of cardiovascular health, we similarly compare LE8 scores from baseline to 6 months with a linear mixed model approach as previously described. Following published guidelines, the LE8 metric is summed into a 1-100 score [17,45]. In addition to comparisons of mean scores at baseline and 6 months post partum, changes in group mean scores across this period are compared (ie, the interaction between treatment and time, eg, heart health score from baseline to 6 months post partum in the intervention vs attention control participants). Components of the LE8 score include diet, physical activity, tobacco use, sleep, weight, cholesterol, blood glucose, and BP—each of the 8 elements is scored separately, and a summary score is created. An 80 or higher on the LE8 metric is considered ideal, with 50-79 being intermediate, less than 50 meaning poor, with a range of 0 (poor) to 100 (ideal). Prior work shows a 10-point change is considered clinically meaningful [46].

For both primary end points, given the longitudinal nature of the intervention, dose is an important effect for exploration. Additionally, we model a site (ie, hospital) effect as a fixed main effect and explore a site by treatment interaction (eg, given the potential for personnel [ie, doula] differences across sites, there is potential for a site-level difference in treatment response).

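### Covariates for both primary mixed models are picked from the trial data, and baseline EPDS and LE8 are not fixed as adjustment terms, which costs prespecification and precision

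*Protocol article*

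**What the plan says.** All of this stands in the protocol article, under Statistical Analysis: Analysis of the Dual Primary End Points.

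- **Baseline tests.** A preliminary analysis "examines baseline characteristics between study arms (LHMoms intervention vs attention control) to verify that the randomization generated comparable groups". It uses chi-square or Fisher tests and t or Wilcoxon tests, with significance at P<.05.
- **Covariate rule.** "Baseline characteristics associated with PPDS in univariate regression models (eg, parity) or group imbalance detected at baseline are included in linear mixed models". Parity is only an example. No candidate list is given, and no threshold for counting as associated.
- **EPDS model.** A linear mixed model is used to "make group comparisons between the LHMoms intervention and attention control at baseline and 6 months post partum".
- **LE8 model.** For the second primary outcome, "we similarly compare LE8 scores from baseline to 6 months with a linear mixed model approach as previously described". The section then adds: "In addition to comparisons of mean scores at baseline and 6 months post partum, changes in group mean scores across this period are compared". The change comparison is identified as the interaction between treatment and time.
- **Site.** For both endpoints, "we model a site (ie, hospital) effect as a fixed main effect and explore a site by treatment interaction". This is the only adjustment term fixed in advance.

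Baseline EPDS and baseline LE8 are scheduled for every participant (Data Collection, Table 3), but neither is named as a covariate.

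**The concern.** This is a rule that the article states, so it cannot be treated as detail left to an analysis plan. A plan that followed it would inherit the problem, and a plan with a fixed list would contradict it.

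The rule has two entry routes, and both are poor. Screening against PPDS means that the primary model is unknown until outcomes have been examined. Screening on imbalance tests chance, because any difference between properly randomized arms arises by chance, and a small P value says nothing about whether the variable predicts the outcome. For LE8 there is a further mismatch: the inherited screen is association with depressive symptoms, not with cardiovascular health.

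The covariate most likely to be useful for each endpoint, its own baseline value, has no guaranteed place as an adjuster. At stake are a primary model that can be named before the data are seen, and precision that the trial could have from data it already collects.

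**Working it through.** The article gives no figure for this point, so there is none to reproduce. The number of baseline characteristics and the correlation r between baseline and 6-month scores are assumptions, because the article states neither.

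**1. Chance flags from the baseline tests.** With k independent characteristics each tested at 0.05, P(at least one flag) = 1 − 0.95^k.

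| k (assumed) | P(at least one flag) |
|---|---|
| 8 | 0.34 |
| 10 | 0.40 |
| 15 | 0.54 |
| 20 | 0.64 |

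**2. What the stated contrasts estimate.** Take a mixed model with baseline and 6-month scores as repeated outcomes, free means by arm and time, and complete data. Its 6-month contrast is the plain difference in 6-month means, and its treatment-by-time contrast is the difference in mean change. Neither is baseline-adjusted in the ANCOVA sense unless the baseline score is a covariate or the baseline means are constrained equal across arms. The article states neither device.

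**3. Precision of the three contrasts.** With equal variances at both times, and the unadjusted 6-month contrast set to 1, the change contrast has variance 2(1 − r) and the baseline-adjusted contrast 1 − r². The ratio of adjusted to change is (1 − r²)/[2(1 − r)] = (1 + r)/2.

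| r (assumed) | Unadjusted 6-month | Change | Baseline-adjusted | Reduction vs unadjusted | Reduction vs change |
|---|---|---|---|---|---|
| 0.4 | 1 | 1.20 | 0.84 | 16% | 30% |
| 0.5 | 1 | 1.00 | 0.75 | 25% | 25% |
| 0.6 | 1 | 0.80 | 0.64 | 36% | 20% |

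These ratios apply to continuous scores. They do not carry over to the article's sample-size calculation, which compares proportions.

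**4. Simulation of the rule.** Assumptions: 450 participants, 15 standardized candidate covariates, r = 0.5, entry at P<.05 by either route, 3000 runs per scenario. A regression of the 6-month score stood in for the mixed model, and the baseline score was not in the candidate pool.

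- With 3 of the 15 candidates truly prognostic, about 4.1 covariates entered per trial, and over 300 different covariate sets arose in 3000 trials.
- Applied mechanically with no treatment effect, the rule rejected in 4.6% of trials (3 prognostic candidates) and 5.1% (none prognostic). The simulation error is about √(0.05 × 0.95/3000) = 0.4 percentage points, so both agree with 5%.
- Taking the smallest P value of four analyses (unadjusted, screened covariates, change, baseline-adjusted) rejected in 11% and 10% of trials.
- With a true effect of 0.25 SD and 3 prognostic candidates, power was 87% with prespecified baseline adjustment, 79% with screened covariates and no baseline, 76% with change and 75% unadjusted.

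**The case against.** Several counterarguments have force.

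- **Error rates.** A reader might infer that the rule makes type I error and confidence intervals unreliable. The simulation does not bear this out when the rule is followed mechanically. The 10% to 11% figure needs an analyst who picks the best of four analyses, one of which (baseline-adjusted) the article does not name. The article also says that analysts are blinded to condition (Abstract and Results), and screening against PPDS can be run on pooled data without arm labels. Blinding limits choice in favor of an arm. It does not fix the model in advance, and it does nothing for the imbalance route.
- **Use of baseline.** A reader might infer that baseline scores are ignored. They are not: they are in the mixed models as repeated outcomes, and the LE8 interaction subtracts baseline by construction. What is missing is baseline adjustment.
- **Baseline EPDS would pass the screen.** For continuous scores with r = 0.4 and n = 450, t = 0.4 × √448/√0.84 ≈ 9.2, so it almost certainly would if it is a candidate. The article does not say that it is, and in a model where it is already a repeated outcome its role as a covariate would have to be defined. Nothing comparable protects LE8, because the screen is against PPDS.
- **LE8 contrast.** The analysis section speaks of determining changes, and Summary and Conclusions hypothesizes greater improvement, so the article leans toward change. It does not rank that contrast against the comparison of 6-month means.
- **Valid estimators.** Change and baseline-adjusted contrasts both estimate the same effect under randomization. The choice between them is one of efficiency, and that is how the point is put here.

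**Conclusion.** The concern stands as one of prespecification and precision. The article states a data-driven entry rule, fixes only site in advance, applies a depression-based screen to a cardiovascular endpoint, and leaves baseline adjustment of both primary scores to chance.

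The chance of at least one spurious imbalance flag is 34% to 64% for an assumed 8 to 20 independent characteristics. For r between 0.4 and 0.6, baseline adjustment lowers variance by 16% to 36% against an unadjusted 6-month comparison, and by 30% to 20% against a change contrast. The first range could be read as worth 19% to 56% more participants (1/0.84 to 1/0.64). That equivalence holds only against an unadjusted comparison of a continuous score. Against change the figure is 2/(1 + r) − 1, which is 43% at r = 0.4 and falls to 25% at r = 0.6, and neither figure transfers to the power for the PPDS proportion.

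Inflation of type I error is not demonstrated and is not part of this conclusion.

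**What to change.** 1. Delete the rule that admits covariates by univariate association with PPDS or by detected imbalance, and delete the significance tests of baseline characteristics. Baseline data by arm can still be described.
2. For each primary endpoint, prespecify the baseline value of that outcome (EPDS for the EPDS model, LE8 for the LE8 model), either as a covariate or by constraining the baseline means equal across arms.
3. Keep site as the fixed main effect already planned, and add any short prognostic list by name, for example parity.
4. State the baseline-adjusted treatment difference at 6 months as the single primary contrast of each mixed model, and report the treatment-by-time change as supportive.

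The cost is wording in the protocol and analysis plan. No new data are needed, because baseline EPDS and LE8 are already scheduled. There is time: the Abstract places the analysis of trial results no earlier than September 2029.

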Participants in LHMoms are randomized to the intervention arm, where participants receive the doula-delivered CBT+cardiovascular health intervention, or the attention control arm, where participants receive a variation of standard doula-delivered postpartum care (based on a community-informed and provider-informed standardized checklist for doula care routinely used by one of our community partners, CWHA). Individuals are enrolled during delivery hospitalization and are consented and connected to their doulas in the hospital, predischarge. The intervention begins within the first week post hospital discharge and continues up to 6 months post hospital discharge. Throughout the 6 months, the intervention arm receives a total of 12 doula-led sessions. The attention control arm also receives a total of 12 doula-led sessions. Sessions for all participants are delivered via Zoom (Zoom Communications, Inc) or phone, based on the participants’ preference. All participants are fitted for and receive a home BP monitoring device and are trained on the correct way to use it before discharge. The LHMoms intervention arm begins with a 7-day emergency detection period, during which doulas contact participants daily within the first week at home to monitor MH and cardiovascular health, as the highest risk of severe maternal morbidity exists during this time period. The LHMoms study design is outlined below in Figure 1. The primary outcomes will be prevention of PPDS and cardiovascular health, measured at 6 months post partum. Doulas are supervised by this study’s psychiatrist or psychologist throughout this study, and all study data is entered into a REDCap (Research Electronic Data Capture) database maintained at the primary study site.

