## Discussion

### Summary and Conclusions

This hybrid type 1 effectiveness- implementation RCT tests a novel nonspecialist intervention to prevent MH and cardiovascular health complications of childbirth. Our design is rigorous—we test the intervention against an attention control and measure numerous secondary outcomes having to do with health care use.

We hypothesize that, compared to attention control participants at 6 months post discharge, intervention arm participants will have at least 31.5% lower incidence of PPDS (score >9 on EPDS), and at least 1-point greater improvement in cardiovascular health using the LE8 score. We also expect that participants randomized to the intervention arm will experience better quality of life, reporting lower perceived stress and substance use and higher rates of resilience and perceived social support. Regarding health care use and satisfaction, we anticipate that more intervention than control individuals will have an indicated health care provider contact within the first 7 days post discharge or attend 6-week postpartum visits. We also hypothesize that intervention participants will report greater patient satisfaction with postpartum care, with higher scores on the CSQ-8 survey than control participants. We have culturally adapted an existing intervention to our local population in NYC, and will also be tracking specifics of implementation that will allow us to adapt the intervention further for other contexts. We will obtain important data from participants and key players in the implementation that will support and inform on the long-term sustainability and scalability of the LHMoms program.

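### The co-primary LE8 endpoint is given both a 6-month mean comparison and a difference-in-change comparison, and neither is named as the primary test

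*Protocol article*

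**What the plan says.** All references are to the Protocol article.

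- **Statistical Analysis: Analysis of the Dual Primary End Points.** The LE8 paragraph opens: "To determine changes in the second primary outcome of cardiovascular health, we similarly compare LE8 scores from baseline to 6 months", using the linear mixed model already set out for the depression endpoint. It continues: "In addition to comparisons of mean scores at baseline and 6 months post partum, changes in group mean scores across this period are compared", and explains the second comparison as "the interaction between treatment and time". Three comparisons are therefore listed for one endpoint: arm means at baseline, arm means at 6 months, and the difference between arms in change. None is called primary or supportive. The same section does mark dose and the site-by-treatment interaction as matters to explore.
- **Summary and Conclusions.** The hypothesis for LE8 is "at least 1-point greater improvement in cardiovascular health using the LE8 score", which is a statement about change.
- **Data Collection, Table 3.** The note on the Heart Score says "My Life Check is only completed in baseline and" the 6-month long surveys, so the full score has two time points.
- **Significance level.** "Statistical significance is set at" P<.05 stands in the paragraph on baseline comparability, and "a 2-sided significance level of 0.05" stands in the sample size section for the depression endpoint. Neither is tied explicitly to LE8.

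**The concern.** With two time points and a separate baseline mean for each arm, the difference in change equals the 6-month difference minus whatever baseline difference chance has produced. The two contrasts then have different estimates, different variances and different P values. The article lists both under a primary endpoint without ranking them, so a reader of the results could not tell from it which one answers the LE8 question when they disagree. If a positive result on either were accepted, the error rate for LE8 alone would exceed 0.05. That is separate from having two primary endpoints.

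The baseline comparison cannot bear on efficacy: between randomised arms, any baseline difference is due to chance.

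**Working it through.** **The plan's own figure.** There is none to reproduce. The article gives no sample size, power or alpha specific to LE8.

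**Inputs.** The contrasts and the two time points come from the sections cited above. Two-sided 0.05 is the level stated for the depression endpoint and is applied to LE8 here as an assumption. The correlation rho between baseline and 6-month LE8 is not in the article, so 0.3 to 0.8 is assumed. Equal variances at both visits, complete pairs and no covariates are also assumed.

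**Step 1: how the two tests relate.** Let b and f be the arm differences at baseline and 6 months, each scaled to variance 1, with correlation rho.
- Var(f − b) = 2(1 − rho)
- Cov(f, f − b) = 1 − rho
- Corr(f, f − b) = (1 − rho)/√(2(1 − rho)) = √((1 − rho)/2)

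At rho = 0.5 this is √0.25 = 0.5. The tests are positively correlated but far from identical.

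**Step 2: false-positive rate if either could support a claim.** This is P(|Z1| > 1.96 or |Z2| > 1.96) under the null, from the bivariate normal distribution. P(both) = 0.10 − P(either), and the tests disagree with probability P(either) − P(both).

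| rho | correlation of tests | at least one significant | disagree under the null |
|---|---|---|---|
| 0.3 | 0.592 | 8.8% | 7.6% |
| 0.5 | 0.500 | 9.1% | 8.2% |
| 0.7 | 0.387 | 9.4% | 8.7% |
| 0.8 | 0.316 | 9.5% | 9.0% |

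Two independent tests would give 1 − 0.95² = 9.75%. These null results do not depend on the LE8 SD. Keeping both contrasts at an overall 0.05 would need about 0.026 to 0.028 for each.

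**Step 3: disagreement when there is an effect.** Take an illustrative effect that gives the 6-month contrast 80% power at 225 per arm. The two contrasts then reach different significance decisions in 27%, 23%, 20% and 20% of simulated trials at rho 0.3, 0.5, 0.7 and 0.8. With an assumed SD of 10 to 15 points, this effect is 2.8 × SD × √(2/225), or about 2.6 to 4.0 points. It shows that the tests differ; it is not a forecast for this trial.

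**Step 4: precision of a merged contrast.** With a common baseline mean, or with adjustment for baseline LE8, there is one estimate. Its large-sample variance is proportional to 1 − rho², against 1 for the 6-month difference and 2(1 − rho) for the change.

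| rho | 6-month difference | difference in change | common baseline |
|---|---|---|---|
| 0.3 | 1.00 | 1.40 | 0.91 |
| 0.5 | 1.00 | 1.00 | 0.75 |
| 0.7 | 1.00 | 0.60 | 0.51 |
| 0.8 | 1.00 | 0.40 | 0.36 |

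Because 2(1 − rho) − (1 − rho²) = (1 − rho)², which is positive for rho below 1, the merged estimate beats the change contrast. For rho other than 0 it also beats the 6-month difference.

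**The case against.** A reader might infer that LE8 has two deciding tests and so two chances at 0.05. The article does not say that. It describes several outputs of one mixed model, never states that either alone is enough, and does not attach 0.05 to LE8. The rates in Step 2 show what would follow if that were allowed, not what the plan prescribes.

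A reader might also see a contradiction with Study Overview, which says: "The primary outcomes will be prevention of PPDS and cardiovascular health, measured at 6 months post partum". That is a statement of timing for both endpoints, and a change from baseline to 6 months is also measured at 6 months. Nor does Table 6 add a third primary contrast: its percentage change in LE8 is an implementation measure under the tertiary end points.

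The text leans to change. The LE8 paragraph opens with it, cites a 10-point change as clinically meaningful, and the hypothesis concerns improvement. This stands, and it is why the fix adopts change. But an opening phrase and a hypothesis in the Discussion do not rank two comparisons joined by wording that makes one an addition to the other.

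Two further objections stand in part. First, naming the primary contrast is often left to a statistical analysis plan, which may exist and may settle this. The point here rests on what the article itself lists without ranking. Second, the article gives no parameterisation, and it lets characteristics imbalanced at baseline enter the models as covariates. Free baseline means are therefore inferred from the planned baseline comparison. Covariates chosen after an imbalance is detected are not the same as a fixed plan to constrain or adjust for baseline LE8.

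**Conclusion.** The point holds as a lack of ranking, not as a demonstrated error-rate failure. The article lists non-equivalent LE8 comparisons under a co-primary endpoint and leans to change without making it the rule. If baseline means are free by arm, the 6-month and change contrasts can disagree. If either could support a claim at two-sided 0.05, the LE8 false-positive rate would be about 9% (8.8% to 9.5%) under the assumed correlations of 0.3 to 0.8. With one contrast named, it is 0.05. The precision gain in Step 4 does not depend on how the results would be claimed, so the change is worth making even if the authors always meant the interaction to decide. Attrition, site terms and clustering by doula would alter the exact figures.

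**What to change.** State that the single primary LE8 contrast is the between-arm difference in change in LE8 from baseline to 6 months. Estimate it in a mixed model with a common baseline mean for the two arms, or equivalently in a model adjusted for baseline LE8. The 6-month difference and the difference in change then coincide, with one estimate and one P value. Remove the between-arm baseline test from the primary analysis, and label all other LE8 comparisons supportive.

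The cost is one or two sentences in the analysis section or statistical analysis plan and a small change to the model specification. No data collection or participant is affected, and the article schedules analysis from September 2029, so it can be settled before then. Naming the interaction alone would remove the ambiguity, but not gain the precision.
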